### Outcomes

2.11

#### Main Outcomes

2.11.1

##### Structure of the intestinal flora

2.11.1.1

Feces samples from 3 groups of children will be collected and stored at −80 °C. Total genomic DNA will be extracted from all feces samples using commercial DNA purification kits as per the manufacturer's recommendations. Samples will be stored at −20 °C after qualitative detection. Concentrations will be determined through 0.8% agar-gel electrophoresis. For the detection of the 16S rRNA V6 region, the upstream primer 967F (CNACGCGAAGAACCTTANC) and downstream primer 1046R (CGACAGCCATGCANCACCT) will be used for all amplification reactions. The amplification system was 25uL, Takara Ex Taq was used, and the template was 2 uL. Amplification conditions will be as follows: 94 °C for 2 minutes; 94 °C for 30 seconds; 57 °C for 30 seconds; 72 °C for 30 seconds (× 30 cycles); final extension of 72 °C for 5 minutes.

#### Short chain fatty acids *(*SCFAs*)* assays

2.11.2

The levels of SCFAs in the feces of each group will be determined using the GC method. Briefly, 0.5 g of each sample will be added to 4 mL of diluent, consisting of 15 mL of 100 mmol/L 2-ethyl butyrate and 50 mL of 5 mmol/Ld hydrochloride through spiral blending. Samples will be centrifuged at 4000 r/min for 10 minutes, and 1 mL subjected to ether extraction 3 times. It will then be added to internal standard solutions (10 μL) and right amount of anhydrous sodium sulfate, and the ether will be transferred to a small bottle containing a plug in a ventilated environment to aid evaporation. Samples will be covered and stored at 4 °C prior to testing. According to the standard curves of each acid, the content of SCFAs in each sample will be calculated from meteorological chromatographic charts.

#### Secondary outcomes

2.11.3

Serum trace element levels, including Zn, Fe, and Ca will be measured by ICP-AES. Hemoglobin levels will be determined using resistive methods. Excretion rates of D-xylose in the urine will be determined using the reduction method. Gastric emptying and motility will be assessed using Color Doppler Ultrasonography.

#### Complications and adverse events

2.11.4

All adverse events will be monitored during the assigned intervention and throughout the study period. Adverse events related to massage and oral medication, such as flatulence, abdominal pain, and increased bowel motility due to medication will be reported to the appropriate regulatory authority.

#### Data management

2.11.5

All data will be recorded independently by 2 trained research assistants in the form of case report forms. All information will be kept strictly confidential. Since the known risks of massage are minimal, formal data monitoring committees are not required for data collection. The study will be regularly monitored and reviewed by independent investigators within the hospital staff.

#### Statistical analysis

2.11.6

SPSS22.0 statistical software will be used for all analysis. Data will be graded using rank sum tests. *χ*^2^ tests will be used for data counts. Measurement data will be shown as the mean ± standard deviation. Data with a normal distribution will be analyzed using a 1-way analysis of variance. Least Significant Difference tests will be adopted for parity of variance. A Games–Howell test will be adopted for data with a non-normal distribution. The rank sum test was used for those who did not conform to normal distribution. *P* < .05 will be considered statistically significant.

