**Methods::**

A total of 60 healthy children will be randomly selected for physical examination. According to a random number generated by a computer, children with anorexia who meet the inclusion criteria will be selected. In strict accordance with the time sequence of inclusion, subjects will be randomly assigned to either the massage or control group (n = 60 per group). The blank group will receive no treatment. Children in the massage group will receive a designated massage protocol. The control group will be administered oral Jianweixiaoshi tablets over 4 weeks. Each group will be compared for intestinal flora structure, fecal short chain fatty acids levels, serum trace elements, urine D-xylose-excretion rates, gastric fluid emptying, gastric motility, and hemoglobin levels before and after treatment.

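### The main flora outcome has no named test variable, yet all analysis is fixed to one-variable-at-a-time tests at a single unadjusted P < .05

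*Protocol article*

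**What the plan says.** - **Main outcome.** Under Main Outcomes (2.11.1) the article lists "Structure of the intestinal flora". The method is sequencing: "For the detection of the 16S rRNA V6 region, the upstream primer 967F" and its partner primer. The text stops at the amplification conditions and names no derived variable.
- **SCFAs (2.11.2).** "The levels of SCFAs in the feces of each group will be determined using the GC method". Each acid has its own standard curve, so this outcome is also several variables.
- **Secondary outcomes (2.11.3).** "Serum trace element levels, including Zn, Fe, and Ca will be measured by ICP-AES". Hemoglobin, D-xylose excretion, gastric emptying and gastric motility follow.
- **Comparison (Abstract, Methods).** "Each group will be compared for intestinal flora structure, fecal short chain fatty acids levels, serum trace elements" and the remaining measures, before and after treatment.
- **Analysis (2.11.6).** "SPSS22.0 statistical software will be used for all analysis". The tests listed are rank sum, chi-square and one-way ANOVA, with Least Significant Difference (LSD) or Games-Howell comparisons. One rule covers everything: P < .05 "will be considered statistically significant". No community-level test and no adjustment across variables is mentioned.

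**The concern.** A 16S profile is a vector of relative abundances over many taxa. Each listed test takes one variable at a time, so to use it someone must first reduce the profile to a scalar, or else test taxa separately. The article does neither explicitly. The index, taxonomic level or taxon could therefore be chosen after the data are seen, with every choice judged at .05. The same freedom exists for the SCFAs, where any single acid could be put forward.

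This matters because flora is the purpose of the trial: the abstract's conclusion expects the study to confirm how massage acts through the flora and host metabolism. A significant result found by an open search at .05 could not carry that claim.

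**Working it through.** **Is there a figure in the plan to reproduce?** No. The only error rate stated is the .05 threshold in 2.11.6. The number of taxa and the number of acids are not given.

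**Does any listed procedure control error across variables?**
- One-way ANOVA is an omnibus test across groups, for one variable.
- LSD leaves the pairwise tests unadjusted. In a simulation of three null groups of 60 (40,000 runs), the chance of any false pairwise difference on one variable was 12.2% ungated and 5.1% when a significant ANOVA was required first. The article does not state that gate.
- Games-Howell adjusts the group contrasts within one variable only.

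So there is at best control within a variable, and none across taxa, acids or the two main outcomes.

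**Chance of at least one false positive across k features.** Assume all k are null, one contrast is tested, and each test is at .05. With independence:

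FWER = 1 − (1 − 0.05)^k, and expected false positives = 0.05 × k.

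| k (assumed) | FWER | Expected false positives |
|---|---|---|
| 1 | 5.0% | 0.05 |
| 2 | 9.75% | 0.10 |
| 10 | 40.1% | 0.5 |
| 20 | 64.2% | 1.0 |
| 50 | 92.3% | 2.5 |

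The row k = 2 is the best case for the two main outcomes: one flora variable and one SCFA variable, unadjusted. FWER first passes 95% at k = 59, since ln(0.05)/ln(0.95) = 58.4.

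**Effect of correlation.** Taxa are not independent. The check used equicorrelated normal statistics, z_j = √ρ·z_0 + √(1−ρ)·e_j, rejecting when |z_j| > 1.96, with 20,000 runs:

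| k | ρ = 0.3 | ρ = 0.5 | ρ = 0.8 |
|---|---|---|---|
| 10 | 35% | 29% | 17% |
| 20 | 54% | 42% | 23% |
| 50 | 80% | 62% | 30% |

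Equal positive correlation is a simplification, but it shows the range. At k = 50 and ρ = 0.8 the rate is still 30%/5% = 6 times nominal.

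**After the fix.** One prespecified flora test and one SCFA test under Holm hold the family-wise error for the main outcomes at no more than 5%.

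**The case against.** **This may be left to the SAP.** The article is condensed and the SAP is not shown. The sequence processing, the derived variable and the lead test could sit there, and the software sentence may be generic wording that does not exclude a separate bioinformatics step. This has weight for the missing detail: silence alone would not be a finding. But section 2.11.6 is not silent. It claims its software and test list for every analysis and sets a single threshold. An SAP with a community-level test or error control would depart from that text.

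**Univariate tests can be valid here.** This stands. ANOVA or a rank sum test is sound for one prespecified scalar, such as a diversity index. A reader might infer that the listed tests can only be run taxon by taxon, or that the main question cannot be validly tested at all. Neither follows. The gap is that no variable is named.

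**The large figures rest on assumed counts.** This also stands. A reader might infer that false-positive taxa are nearly certain. The documents do not say that taxa will be tested individually, at what level, or how many. Exceeding 95% needs about 59 or more independent null taxa, correlation lowers the rate, and a single index gives 5%.

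**Pooling all outcomes overstates the problem.** Counting flora and SCFAs once each plus the seven secondary measures gives 1 − 0.95^9 = 37%. The article separates main from secondary outcomes, and the fix leaves the secondary ones unadjusted, so that family is not the right measure of this defect.

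**Conclusion.** The point holds in this form: the article names no testable variable for its multivariate main outcome, treats SCFAs as several acids without a summary, and binds all analysis to univariate tests at one unadjusted .05. This is a stated rule that fits the main outcome badly, not merely detail deferred to an SAP.

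The inflation is conditional. Across the scenarios shown, it runs from none (one index, judged alone) through about 10% (one test for each main outcome, unadjusted) to 92% (50 independent null taxa), with 30% to 80% at 50 correlated taxa. The counts and correlations are assumptions. What needs no assumption is that nothing in the analysis section limits which of these cases will apply.

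**What to change.** Before any outcome data are analysed, amend section 2.11.6 as follows:

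1. Name one lead flora test for massage versus control, the randomised contrast. Use either a global composition test, such as PERMANOVA on a stated between-sample distance, or a baseline-adjusted analysis of one stated diversity index. Fix the distance or index and the taxonomic level in advance.
2. Name one SCFA summary, such as total SCFA, for the same contrast.
3. Apply Holm across these two tests at an overall .05: the smaller P value is compared with .025 and, if it passes, the other with .05.
4. Label taxon-level and single-acid tests exploratory, with Benjamini-Hochberg false-discovery-rate control.
5. Report the secondary outcomes as supportive.
6. Allow software suited to the flora analysis alongside SPSS.

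Other packages of one lead test plus error control would also serve. What is essential is that the lead variables and the error rule are fixed in advance. No new samples or visits are needed. The cost is plan wording, a little more analysis work, and fewer nominally significant taxa to report.

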## Introduction

1

Feeding disorders fall into 3 categories under the Chatoor criteria:^[1]^

(1)feeding disorders of state regulation;(2)feeding disorders of reciprocity; and(3)pediatric anorexia (PN).

PN refers to children with a sustained loss of appetite, who eat less and/or dislike eating. As a disorder of chronic hunger, PN is common in children, with a prevalence of 5% to 10%.^[2]^ The disease is most common in children aged 1 to 5 years.^[3]^ If left untreated, PN can result in childhood malnutrition, body wasting, rickets, anemia, and a decline in immune function, all adverse consequences that can affect growth and development both physically and intellectually, in addition to mental illness.^[4–5]^ In modern medicine, the main treatment for PN is drug treatment, including the use of supplementary trace elements to enhance peptin levels and gastric dynamics^[6]^ However, it is often difficult to determine the exact cause of anorexia in children.^[7]^ Due to the poor compliance of children on oral drugs and the high occurrence of side effects,^[8]^ their clinical application is limited.

As a painless and non-drug therapy, infantile massage is widely applicable to the pediatric disease spectrum, with the advantages of simple operation and a comfortable experience. In clinical practice, massage represents a dominant therapy for PN. Through many years of clinical practice, it has been shown that children with anorexia who receive massage therapy not only significantly improve their appetite, but relieve sallow complexion, abdominal distension, and other accompanying symptoms. Modern medical studies have shown that massage therapy can increase vagus nerve activity and promote appetite regulatory factors, thus increasing gastrointestinal peristalsis^[9]^ and improving digestive function. Massage intervention also correlates with improves the correlation between the brain and intestine axis, intestinal flora activity, and the regulation of host metabolism.

In this study, we explore the biological mechanism(s) of anorexia from the perspective of intestinal flora and the regulation of host metabolism. We further reveal the action site and therapeutic mechanism(s) of pediatric massage for the treatment of anorexia. This furthers our understanding of the optimal treatment methods for the treatment of PN in the clinic.

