### Inclusion criteria

2.3

All subjects will be required to meet the known diagnostic criteria for anorexia in children.^[1]^ The criteria include

(1)a refusal to eat adequate amounts of food for at least 1 month;(2)a failure to communicate hunger and a lack of interest in food;(3)significant growth deficiency;(4)a refusal to eat that is unrelated to an underlying medical illness or a traumatic event;(5)aged 2 to 12;(6)agree to receive massage therapy;(7)consent to the study either directly or through a legal guardian.

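### Before treatment, the stated pairwise tests compare each randomised arm separately with the healthy children (60 v 60), where one contrast of all 120 children with anorexia against the 60 healthy children would be more precise and give one answer

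*Protocol article*

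**What the plan says.** The Introduction gives two linked aims. The first concerns the disease: "we explore the biological mechanism(s) of anorexia from the perspective of intestinal flora and the regulation of host metabolism". The second concerns how massage acts on it.

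The design has three groups. The abstract (Methods) describes the healthy group, "A total of 60 healthy children will be randomly selected for physical examination", and the two treated arms: "subjects will be randomly assigned to either the massage or control group (n = 60 per group" in each case. Section 2.7.2 leaves the healthy (blank) group untreated. Both randomised arms come from one eligible population, since section 2.3 opens with "All subjects will be required to meet the known diagnostic criteria for anorexia in children".

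All three groups contribute to the main outcome (section 2.11.1.1): "Feces samples from 3 groups of children will be collected". The abstract compares the groups at two times. Its sentence begins "Each group will be compared for intestinal flora structure, fecal short chain fatty acids levels" and ends "gastric fluid emptying, gastric motility, and hemoglobin levels before and after treatment".

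For measurement data, section 2.11.6 states "Data with a normal distribution will be analyzed using a 1-way analysis of variance". It then names LSD tests for equal variances, Games-Howell tests, and a rank sum test for non-normal data, with significance at P < .05. It does not say whether LSD is run only after a significant F test. It names no contrast that combines the two randomised arms.

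**The concern.** The healthy children are neither randomised nor ill, so they cannot inform the choice between massage and tablets. Their evident use is as the reference that shows what is abnormal in anorexia. That comparison is cleanest before treatment, because afterwards an arm-versus-healthy difference mixes disease with treatment.

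At baseline the massage and tablet arms differ only by chance. LSD and Games-Howell nevertheless treat them as two separate groups, so anorexia versus healthy becomes two 60 v 60 tests. Two things are at stake. Each test is less precise than the data allow. The two tests can also disagree, so that one arm is reported as differing from healthy children and the other not, although both sample the same population. A reader could take such a split for a real baseline difference between the arms.

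**Working it through.** The article gives no sample-size calculation, effect size or SD, so there is no stated figure to reproduce.

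**Inputs from the article:** 60 healthy, 60 massage and 60 tablet children (abstract, section 2.8); one-way ANOVA with pairwise follow-up and P < .05 (section 2.11.6).

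**Assumptions:** two-sided testing; a common SD; an approximately normal measurement, such as one SCFA concentration; no true difference between the randomised arms at baseline; true anorexia-versus-healthy differences d of 0.3 to 0.6 SD.

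**Precision, in SD units**
- One arm v healthy: variance = 1/60 + 1/60 = 0.0333; SE = 0.183.
- Both arms v healthy: variance = 1/120 + 1/60 = 0.0250; SE = 0.158.
- Information in a pairwise contrast relative to pooled: 0.0250/0.0333 = 0.75, that is 25% less.
- Confidence interval width, pooled relative to pairwise: √0.75 = 0.866, about 13% shorter.
- Difference detectable with 80% power: (1.96 + 0.84) × SE = 0.51 SD pairwise and 0.44 SD pooled.

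The 25% depends on equal SDs. If the SD in anorexia were twice that in healthy children, the ratio would be (4/120 + 1/60)/(4/60 + 1/60) = 0.60, a 40% loss. If the healthy SD were twice as large, it would be (1/120 + 4/60)/(1/60 + 4/60) = 0.90, a 10% loss.

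**Power.** The t tests use the noncentral t distribution with noncentrality d/SE. The F test has 2 and 177 degrees of freedom and noncentrality 60 × d² × 2/3, which is 8.1 at d = 0.45.

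| d (assumed) | one arm v healthy | overall F | pooled 120 v 60 |
|---|---|---|---|
| 0.30 | 37% | 37% | 47% |
| 0.40 | 59% | 61% | 71% |
| 0.45 | 69% | 72% | 81% |
| 0.50 | 78% | 81% | 88% |
| 0.60 | 90% | 93% | 97% |

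The F test uses all 180 children but still has less power than the pooled contrast. One of its two degrees of freedom goes to massage versus tablets at baseline, where randomisation makes the true difference zero.

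**Contradictory answers.** This is the simulated share of trials in which exactly one arm differs significantly from healthy under LSD (error df 177).

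| d (assumed) | LSD without an F gate | LSD only after a significant F |
|---|---|---|
| 0.30 | 31% | 16% |
| 0.40 | 32% | 19% |
| 0.45 | 29% | 18% |
| 0.50 | 24% | 16% |
| 0.60 | 13% | 9.5% |

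At d = 0.45, both arms are significant after a significant F in 54% of trials. With the studentized-range critical value that Games-Howell uses, the arms disagree in 33%.

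**Error under no disease difference.** The chance that at least one arm is declared different from healthy is 9.1% for ungated LSD, 4.2% for LSD after a significant F, and 3.6% with the studentized-range critical value.

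**The case against.** The strongest reply is that the article never formulates an anorexia-versus-healthy hypothesis and assigns no test to one. The abstract's conclusion and the Discussion put the weight on what massage does to flora and metabolism. Naming a particular contrast is often left to a statistical analysis plan, which is not shown. This stands in part: the disease question is an inference from the stated aim and the presence of a healthy group. But section 2.11.6 is not silent on method. It names an omnibus test and two pairwise procedures, and at baseline these fit that aim less well than a contrast that costs nothing.

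The ANOVA sentence itself also describes the overall F test on all 180 children, not two 60 v 60 tests. That is correct. The pairwise contrasts come from the follow-up tests named directly after it. No data are discarded either: the LSD error variance uses all three groups, and the average of the two arm-versus-healthy differences is exactly the pooled difference. The loss therefore belongs to each pairwise contrast and not to the analysis as a whole.

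A reader might infer that asking the question twice nearly doubles its false-positive chance. The document does not support this. The figure of about 9% needs LSD run regardless of the F test, which section 2.11.6 does not state. With the F gate the chance is about 4%, and Games-Howell already adjusts for multiplicity.

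**Conclusion.** The point holds as an efficiency and clarity improvement for the baseline disease comparison. Each pairwise contrast carries 25% less information than the pooled one if the SDs are equal. At an assumed 0.45 SD, power is 69% against 81%, with the overall F test in between at about 72%. Disagreement between the arms is a real risk: about 18% of trials with gated LSD and 29% without a gate at that effect size. All power and disagreement figures rest on assumed effects, because the article gives none.

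Two stronger readings should be resisted. The trial as a whole does not lose a quarter of its information. The randomised massage-versus-tablet comparison is not weakened either, because the point concerns only a non-randomised baseline comparison. After treatment the arms have been treated differently, so keeping them separate is then appropriate.

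**What to change.** In section 2.11.6, state that anorexia versus healthy is assessed by one pre-specified baseline contrast: all 120 randomised children together against the 60 healthy children, for the flora measures and SCFAs. Keep this apart from the post-treatment comparison of massage with tablets. Say that any post-treatment comparison of an arm with the healthy group is reported only as a description of normalisation, not as a test of the disease question.

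In SPSS this is a planned contrast in the same one-way model, with weights ½, ½ and −1, or a two-group test after combining the arms (a two-group rank sum test where the data are not normal). The cost is a few lines of wording, with no additional children, samples or visits. If an analysis plan already contains this contrast, it is enough for the article to refer to it.

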### Randomized grouping

2.8

A total of 60 healthy children will be randomly selected for physical examinations. A statistical expert not involved in the design of the study will use SPSS 22.0 software to generate a series of random sequences, which will be marked onto a card and placed in a sealed envelope. Each subject will receive an envelope at a time-point consistent with the test conditions. Subjects will be randomly divided based on their number into control or test groups (n = 60 per group). For each child, the chiropractor will open the envelope to obtain the grouping code.

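### Section 2.11.6 sends non-normal data both to Games–Howell, an unequal-variance method, and to the rank sum test, and gives normal data with unequal variances no pairwise procedure

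*Protocol article*

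**What the plan says.** Section 2.11.6 of the protocol article chooses tests by the distribution of the data. For normal data: "Data with a normal distribution will be analyzed using a 1-way analysis of variance". This sentence sets no condition on the variances. For the pairwise step under equal variances: "Least Significant Difference tests will be adopted for parity of variance". Two sentences on non-normal data follow directly: "A Games–Howell test will be adopted for data with a non-normal distribution", and then "The rank sum test was used for those who did not conform to normal distribution". Significance is set at 0.05. No sentence names a procedure for unequal variances, and no other section returns to the question.

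The rule serves three groups of 60: the massage and control arms, which are randomised, and a blank group of healthy children (section 2.8). The main outcomes are the structure of the intestinal flora and fecal SCFAs (section 2.11).

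**The concern.** There are two faults. First, the two sentences on non-normal data attach different tests to the same condition. The tests address different hypotheses (means against ranks) and control error differently: Games–Howell builds in an adjustment for the number of groups, while no adjustment is stated for the rank sum test. Second, Games–Howell is attached to the wrong condition. It is the natural partner of LSD when variances differ, and that situation is left without a pairwise procedure.

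An analyst who follows the section faithfully could therefore report either of two P values for the same non-normal outcome. If a main outcome falls in that branch, the trial's conclusion could depend on which sentence was followed.

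**Working it through.** The plan gives no SD, effect size or power for any outcome, so there is no figure to reproduce. The check has three steps.

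**1. The rule as a decision table.**

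| Data | Overall test | Pairwise test |
|---|---|---|
| Normal, equal variances | one-way ANOVA | LSD |
| Normal, unequal variances | one-way ANOVA | none stated |
| Non-normal | Games–Howell and rank sum both assigned | same conflict |

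The third row is the contradiction and the second is the gap.

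**2. What Games–Howell does.** For groups i and j it computes |mean_i − mean_j| / √[(s_i²/n_i + s_j²/n_j)/2], with Welch degrees of freedom, and refers it to the studentized range for k groups. Separate variances enter the formula. It contains nothing that deals with non-normality, and it still compares means.

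**3. How often the two sentences would disagree.**

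Input from the plan: n = 60 per arm (section 2.8) and level 0.05 (section 2.11.6). Assumed: two-sided tests; log-normal data; log SD of 1, 0.5 and 0.3; a log-shift of half the log SD in each case (0.5, 0.25 and 0.15). Each simulated trial was tested three ways:

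- *Literal reading:* Games–Howell with k = 3 against an unadjusted rank sum test at 0.05.
- *Both unadjusted:* Welch test at 0.05 against rank sum at 0.05.
- *Both adjusted:* Games–Howell with k = 3 against rank sum at 0.05/3 = 0.0167.

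The last two readings put both tests on equal multiplicity terms.

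| Log SD, shift | Different verdicts, equal multiplicity terms | Different verdicts, literal reading |
|---|---|---|
| 1, 0.5 | about 25–27% | 36% |
| 0.5, 0.25 | about 11–14% | 19% |
| 0.3, 0.15 | about 8–10% | 14–15% |

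Separate runs agreed to within one or two percentage points. At log SD 1 the rejection rates were about 41% (Games–Howell) against 76% (rank sum) on the literal reading, 59% against 76% with both unadjusted, and about 40% against 59% with both adjusted.

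**The gap in the second row.** For normal data with no true difference, 60 per group and assumed SDs of 1, 1 and 2, ordinary ANOVA rejects in 6.2% of trials. If the analyst fell back on LSD, its false-positive rate would be 0.5% for the pair with equal SDs and about 8% for each of the other two pairs. Games–Howell gives about 2% per pair and 5.1% for any pair. With equal group sizes the overall test is only mildly affected, and the harm lies in the pairwise comparisons.

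**The case against.** The strongest reply is that this is a slip of wording. If the Games–Howell condition is read as unequal variances, the section becomes orderly: ANOVA, LSD if variances are equal, Games–Howell if not, rank sum if the data are not normal. That is probably what was meant, and it makes this a drafting error and not a defect of design. It does not rescue the published text, which states a different condition. Nor can the two sentences be reconciled as an overall test with its follow-up, because a comparison of means does not follow up a rank test.

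A reader might also infer more than the documents support:

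- *That normal data with unequal variances have no test at all.* The ANOVA sentence covers all normal data. What is missing is a pairwise procedure.
- *That 36% disagreement is the effect of comparing means instead of ranks.* It sets a three-group-adjusted test against an unadjusted one, under the heaviest skew considered. Under the null at log SD 1, the gap between 1.4% and 5.0% rejection is almost wholly that adjustment: unadjusted Welch gives about 4.5%.
- *That the main outcomes are certain to fall in the conflicting branch.* The protocol does not say that flora or SCFA measures are skewed.
- *That the analyst is free to pick the favourable answer.* Section 2.9 blinds the statisticians, which limits choice by direction of result. It does not say which test to report.

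It may also be said that an article condenses a fuller plan. That would excuse silence, but here a rule is stated, and stated wrongly.

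**Conclusion.** The point stands in a limited form. Section 2.11.6 gives Games–Howell the wrong condition, contradicts itself on non-normal data, and leaves normal data with unequal variances without a pairwise procedure. This follows from the text alone and needs no simulation.

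The practical size depends on assumptions. If a main outcome is skewed and log-normal with a moderate shift, the choice between the two sentences changes the verdict in roughly one trial in ten to one in four on equal multiplicity terms, and in up to about one in three on the literal reading under heavy skew. If the main outcomes prove close to normal, the contradiction does not touch them. The correction should still be made before analysis, because it is simple and the ambiguous branch could decide a main result.

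**What to change.** In section 2.11.6, change the condition for Games–Howell from non-normality to unequal variances, preferably with Welch ANOVA as the overall test in that case. Keep the rank sum test as the only rule for non-normal data. For each main outcome, record which branch applies before any group-level result is seen.

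The cost is a few words of text, with no effect on data collection, sample size or participants. Log-transforming SCFAs, using robust-error models, dropping normality pre-tests or adding Dunn comparisons after Kruskal–Wallis would be matters of preference. The defect does not require them.
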